## Abstract

**Introduction:**

Attention deficit/hyperactivity disorder (ADHD) is a prevalent and impairing cluster of traits affecting 2%–5% of children. These children are at risk of negative health, social and educational outcomes and often experience severe difficulties at school, so effective psychosocial interventions are needed. There is mixed evidence for existing school-based interventions for ADHD, which are complex and resource-intensive, contradicting teachers’ preferences for short, flexible strategies that suit a range of ADHD-related classroom-based problems. They are also poorly evaluated. In this study, a prototype intervention comprising a digital ‘toolkit’ of behavioural strategies will be tested and refined. We aim to refine the prototype so that its use is feasible and acceptable within school settings, and to establish whether a future definitive, appropriately powered, trial of effectiveness is feasible. This novel iterative study aims to pre-emptively address implementation and evaluation challenges that have hampered previous randomised controlled trials of non-pharmacological interventions.

**Methods and analysis:**

A randomised iterative mixed-methods case-series design will be used. Schools will be randomised to the time (school term) they implement the toolkit. Eight primary schools and 16–32 children with impairing traits of ADHD will participate, along with school staff and parents. The toolkit will be refined after each term, or more frequently if needed. Small, theory-based and data driven changes hypothesised as relevant across school contexts will be made, as well as reactive changes addressing implementation barriers. Feasibility and acceptability will be assessed through quantitative and qualitative data collection and analyses in relation to study continuation criteria, and ADHD symptoms and classroom functioning will be tracked and visually evaluated to assess whether there are early indications of toolkit utility.

**Ethics and dissemination:**

Ethical approval has been obtained. Results will be presented in journal articles, conferences and through varied forms of media to reach policymakers, stakeholders and the public.

Strengths and limitations of this studyThis study uses an iterative staggered design in order to refine an intervention throughout the research process.Measures of acceptability and feasibility of the intervention and of the ability to evaluate it in a rigorous trial setting will be reviewed against continuation criteria throughout the study.Multiple informants will provide relevant data, including school staff and parents, and data on both positive and adverse outcomes will be captured.However, the iterative nature of the study means that different participants will not receive the same intervention, therefore group-level effects cannot be delineated.Alternate analyses will be used to ascertain whether there are patterns of change in symptoms and functioning that replicate across individuals instead.

## Introduction

Children and young people’s mental health and neurodevelopment (including attention deficit/hyperactivity disorder (ADHD)) is a government priority. In the 2017 green paper, the pivotal role of schools in supporting good mental health was acknowledged. By the end of 2023, >20% of schools across the UK will have a designated mental health lead with the aim of improving access to evidence-based treatments.^1^ Cost-effective, implementable, sustainable evidence-based mental health interventions that can be delivered in schools are therefore urgently needed.

ADHD is a neurodevelopmental disorder affecting 2%–5% of children, characterised by impairing levels of impulsivity, hyperactivity and/or inattention.^2^ Multiple negative life course outcomes are associated with childhood ADHD including high rates of co-occurring mental disorders, accidents, poor educational and occupational attainment and antisocial behaviour.^3^ Other neuropsychiatric disorders and unintentional injury are strongly associated with ADHD, which are the leading cause of years lost due to disability worldwide in those aged 10–24 years.^4^ Costs to the health, education and judicial systems, social services and economic loss are substantial; 24% of the mean annual cost of £5493 is attributable to National Health Service resources.^5^ Pharmacological treatment is available and effective for some, especially in acute management of symptoms, but is not appropriate, acceptable or tolerable for all children.^6^ Response is often partial,^7 8^ with tolerance developing over several years.^9 10^ Even with drug treatment, ADHD causes particular problems in school, resulting in the outcomes described above.^11^ Although ADHD medications have been shown to be effective and safe for the treatment of ADHD in the shorter term,^10^ licensed ADHD medications are controlled drugs and in order to access these families must receive a clinical diagnosis of ADHD, waiting lists for which in the UK are currently backlogged. Medication is not appropriate or preferable for all children with ADHD, and in the UK is not recommended as a first-line treatment for children with traits that are not severe;^12^ and non-pharmacological intervention options that can be used as a precursor, alternative or supplement to pharmacological treatments are important.

ADHD causes problems in the classroom for the child, the teacher and for other children.^13^ Symptoms of ADHD (which are also traits present to varying degrees in all children) make it challenging for a child to sit still, be attentive for sustained periods of time, listen to and follow instructions, or to resist impulses to shout out. Children with ADHD traits may also wander around the classroom or school building, struggle to complete schoolwork and need reminders to know what they are doing. This combination of characteristics is challenging for the child themselves; as they are not consciously able to control their behaviour without learning self-monitoring and regulatory strategies and are often criticised by adults and peers for their involuntary behaviour. It can also be disruptive to the usual mainstream classroom context, and there is a poor fit between the UK mainstream Primary classroom environment and the behavioural characteristics and needs of children with impairing traits of ADHD. Development of an effective school-based intervention for ADHD that overcomes the limitations of previous interventions would be likely to improve health and social outcomes. The limitations of existing school-based non-pharmacological interventions are that they usually require delivery by trained clinicians, are complex and multicomponent: targeting many potential deficits in every child regardless of their individual strengths and weaknesses.^14–16^ ADHD encompasses a wide range of core associated symptoms and functional issues that are seen in the classroom, and existing evidence is unclear about what works for whom, or which aspects of interventions are effective. In combination, this means existing interventions are not feasible or affordable for schools to routinely deliver; they are rarely rolled out in schools and are not followed with high fidelity. There are barriers to school staff identifying evidence-based practices and implementing these with high fidelity as well as adapting to the needs of the individual, and sustaining this over time. Reviews of existing school-based interventions for ADHD have highlighted the potential efficacy of such interventions,^17–20^ and so overcoming the limitations of existing interventions is crucial to provide an implementable, effective school-based intervention for ADHD.

We are in the process of developing an intervention from high-quality evidence, based on theory around behaviour change and ADHD and from a programme of development work including a Delphi survey of key stakeholders. We are following the Intervention Mapping approach^21 22^ to co-create the intervention with key stakeholders in order to adapt the format of evidence-based strategies, targeting both symptoms and associated functional impairments, to overcome key implementation issues in schools.^23^ Intervention Mapping has six steps, and the full process of the toolkit development will be detailed in a subsequent publication, however in brief these are: (1) Creating a logic model of the problem; (2) Defining programme outcomes and objectives and a logic model of change; (3) Programme design; (4) Programme production; (5) Programme implementation plan; and (6) Evaluation plan.^22^ The result will be a ‘toolkit’ of strategies in a modular format, with some core components then a selection of optional modules focusing on a different core outcome, that is designed for Primary school staff to use when working with children with traits of ADHD: the Tools for Schools *FLEX* toolkit. The toolkit modules target outcomes that were shown to be of importance to key stakeholders in a Delphi survey;^24^ including conflict with teachers and peers, paying attention, building self-esteem, and improving planning and organisation.

Given the limitations of existing school-based interventions for ADHD, including limited evidence of effectiveness and difficulty evaluating them in methodologically rigorous randomised controlled trials, it is clear that the toolkit will need to be developed in a way that ensures it is acceptable, useful and feasible for school staff. In addition to this, we must address key features that will allow successful trials of the toolkit in future powered trials so that the strength of evidence for its effectiveness is comparable to other treatments such as medication. Intervention development frameworks such as the Medical Research Council complex intervention guidelines highlight the importance of the development and feasibility phases (rather than prematurely evaluating interventions in large randomised trials); carefully optimising protocols, working closely with the target populations, planning and testing implementation, and assessing the acceptability and feasibility of the toolkit are essential to develop an intervention that can later be tested for effectiveness. The development of the toolkit will therefore take an iterative case-series approach, trialling and modifying successive versions of the prototype in order to meet the study objectives. We have not included a control group or comparison group as the study does not aim to assess effectiveness.

In this protocol we outline plans to conduct the initial evaluation and further development of the Tools for Schools *FLEX* toolkit. As the toolkit is at an early stage of development, we plan to assess the acceptability of the toolkit, and the feasibility of implementing it within the Primary school context in the UK.

### Objectives

The main aims of this feasibility study are to:

Refine the prototype *Tools for Schools FLEX* toolkit so that it is feasible and acceptable to implement in the school setting.Establish whether a future definitive trial of effectiveness is feasible.

Secondary aims are to:

Identify suitable outcome measures to assess core ADHD symptoms, child and teacher well-being, academic progress, and identify an appropriate primary outcome (from these) for a future definitive trial.Develop and test a framework for costing the toolkit, and for assessing cost-effectiveness in a future definitive trial.Assess whether observational measures of behaviour, classroom functioning and teacher-reported ADHD symptoms indicate improvement following use of the toolkit.

## Methods and analysis

### Design

A randomised iterative mixed-methods case-series design will be used. Schools will be the units of randomisation, and will be randomised to the time (school term) when they will use the toolkit. The toolkit will be refined after each school has used it for one term, or more frequently if major issues are highlighted during a school’s use of the toolkit. Small, theory-based and data-driven changes hypothesised to be relevant across the school context will be made, as well as reactive changes addressing barriers to implementation. Randomisation to using the toolkit in different school terms allows for inferences to be made as to whether the intervention is improving outcomes, with consistent improvement following the introduction of the core components enabling researchers to potentially rule out alternative explanations for behaviour change, such as improvement due to other support in place or differences in behaviour across the school year. If baseline symptoms and functioning remain on stable trajectories for children across schools, changing only when the intervention is introduced, this implies it is the intervention rather than an alternate factor stimulating the change. It is a commonly used design for single-subject analyses where the intervention cannot be withdrawn and re-implemented such as in an ABAB design.^25–27^

Eight schools will participate in total in two recruitment cohorts of four (in order to avoid later participating schools having to sign up to the study years in advance); each cohort will enter the study at a different time. Schools in each cohort will then be randomly assigned their individual baseline term in the study using a computerised random sequence generator (see figure 1). The length of the baseline period will be the same for each school (one school term), with schools within each cohort entering their baseline period in different school terms; the term in which the intervention is delivered is therefore staggered across the study (figure 1). This design will allow for refining and adapting the toolkit and its implementation based on ongoing participant feedback, maximising the chances it has of being acceptable and feasible (and therefore suitable for further evaluation in a pilot and then definitive cluster randomised controlled trial) by the end of the study.

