#### Identification and recruitment of eligible children and families

Eligible children will either have a clinical diagnosis of ADHD (as reported by the school or parents), or high symptom levels and will be aged 4–10 years (school years Reception-5) at the first baseline assessment to ensure they will be in primary school for the study duration. Children with ADHD may either have not yet received a formal diagnosis, or their family may not wish to pursue a diagnosis, therefore, children with high symptom levels will be eligible. There are no additional exclusion criteria. Teachers and SENCos will identify students who meet criteria for this indicated group using the Strengths and Difficulties Questionnaire Hyperactivity-Inattention Subscale and the impact supplement.^29^ Teachers of potentially eligible children will be asked by the SENCo to complete this brief screening measure, and if this indicates that a child may have probable ADHD (teacher-reported symptoms being ≥6 and impact ≥1), their parent will also be asked to complete the screen in order to ensure that impairments are noted across more than one setting.^2 30^ Should these combined ratings indicate ‘probable’ ADHD according to the validated algorithm, the child will be eligible for inclusion in the study. Probable ADHD is assigned if the parent-report hyperactivity/inattention score is ≥7 and an impact score of 2 is given, or if the hyperactivity/inattention score is ≥9 and an impact score of at least 1 is reported, and the teacher criteria above are met (see sdqinfo.org for syntax).

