### Sample size

The planning group has advised that to minimise burden of data collection on teachers, each class teacher should have a maximum of one child participant however this may be revised during the course of the study; for example, if a school feels strongly that several children in one class may benefit, or if two eligible children in the same class also have TA support and the teacher wishes both to participate. Estimating that each of the eight participating schools will have 2–4 participating children and teachers, there will be a total of 16–32 child participants, 16–64 parents, and 16–64 teachers and TAs along with eight SENCos. The total sample size will depend on the distribution of participating parents, teachers and TAs and the distribution of eligible children across different classes within schools: table 1 indicates the minimum and maximum sample sizes.

**Table 1 T1:** Sample size minimum and maximum

Participant type	Minimum number	Maximum number*
School	6	8
Children	16	32
Parents or carers	16	64 (ie, 2 parents per child)
SENCos	8	8
Teachers	16	32
TAs	0	32

*Maximum number based on every eligible school recruiting four pupils, each of which have a different class teacher. We anticipate actual numbers of TAs will be lower than the maximum.

SENCo, special educational needs (and disabilities) coordinator; TA, teaching assistant.

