### Procedure

The study will run from September 2022 until January 2025. Data will primarily be collected at the participating schools, however interviews with parents and school staff may take place over the phone, via internet video call, at participants’ homes, or in another location of the participant’s convenience. Baseline length will be one school term. During the baseline phase, the teacher will provide repeated measures of the primary quantitative outcomes: participating children’s ADHD symptoms and classroom functioning. These will be collected every 2 weeks during the baseline period and in the intervention period. This detailed baseline data will capture normal fluctuations in symptoms across the term and response to any school-implemented ‘treatment as usual’ during the baseline phase.

Information on healthcare and education resource use will be collected from children, parents and school staff for each child during the baseline period using a structured survey with open questions to capture any resources not mentioned, and child quality of life will be reported by the child and their parent. Any other support or treatment will not be altered during the study. Each school will then implement the intervention for one school term; two modules from the intervention will each be implemented for 4 weeks. There will be a 10-week follow-up period where detailed qualitative data will also be captured, including asking participants about changes in resource and service use relative to the information they provided at baseline.

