### Quantitative measures

There are two quantitative outcome measures that will be assessed in order to: (1) Determine which would be most suitable as the primary outcome in a future trial and (2) Evaluate whether they make sense and are relevant to those completing the measures. *ADHD symptoms* will be measured using the Strengths and Weaknesses of ADHD Symptoms and Normal‐behavior Questionnaire, based on preferences of the planning group who considered several measures of ADHD symptoms,^33 34^ reported by teachers; and *classroom functioning problem behaviour* subscale measured using the Social Skills Improvement System (SSIS),^35^ that captures social, academic and competing problem behaviours in the classroom environment, reported by parents and teachers. These will be measured every 2 weeks during the baseline and intervention periods and every 3 weeks during the follow-up period. All planned quantitative measures are detailed in a table in the online supplemental material.

Other quantitative measures will be captured to assess whether there is indication of some improvement in the key areas the toolkit aims to target. Measures relating to children include *child dimensional psychopathology*, assessed using the teacher and parent-reported Strengths and Difficulties Questionnaire,^30^ and *child-reported satisfaction with school* using the How I Feel About My School measure.^36^
*Teacher well-being* will be measured using the Warwick‐Edinburgh Mental Wellbeing Scale 14-item Teacher Survey^37^ the Teachers’ Sense of Efficacy Scale,^38^ and the Relationship with Work Survey from the Maslach Burnout Inventory-General Survey,^39 40^ and the social skills and academic competence subscales from the SSIS will be completed by teachers. These will be collected at the beginning and end of the baseline period, at the end of the intervention term and at the end of the follow-up term. Other module-specific measures which are not covered by the above measures will be administered depending on the modules used by each child, for example, the Harter Self-Perception Profile for Children to measure self-esteem.^41^

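### In a school with a summer baseline term, a September change of class teacher would coincide with the start of the toolkit, so teacher ratings there cannot separate a new rater from an effect

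*Protocol article*

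**What the plan says.** The phases are tied to terms. Under Design: "The length of the baseline period will be the same for each school (one school term". Under Procedure: "Each school will then implement the intervention for one school term". Follow-up comes next, and Table 3 draws all three phases as 13-week terms. Within each cohort of four schools the start is staggered, "with schools within each cohort entering their baseline period in different school terms; the term in which the intervention is delivered is therefore staggered".

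On who rates, Procedure says that "the teacher will provide repeated measures of the primary quantitative outcomes: participating children’s ADHD symptoms and classroom functioning". Quantitative measures has the SWAN reported by teachers only, and describes the SSIS problem behaviour subscale as a measure "that captures social, academic and competing problem behaviours in the classroom environment, reported by parents and teachers". The same part of the article plans classroom observation by trained researchers.

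On the school year, eligibility stops at Year 5 at the first baseline assessment, "to ensure they will be in primary school for the study duration". So a move up a year during participation was foreseen. The footnote to Table 1 nevertheless allows one class teacher per child: "Maximum number based on every eligible school recruiting four pupils, each of which have a different class teacher".

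On inference, Design says that if trajectories are stable across schools and shift only when the toolkit arrives, this points to the toolkit and not to another cause. The article as shown has no rule for a change of rater.

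**The concern.** A phase boundary is always a term boundary, and one term boundary in three is the start of a school year. If the class teacher changes then, a school whose baseline is the summer term gets a new rater, a new class and a new teacher-child relationship at the moment the toolkit is introduced. A more lenient new rater produces the step that the design looks for; a stricter one hides a real benefit. For that child, nothing in the teacher ratings can tell the two apart.

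At stake is Subaim C, which asks whether teacher-reported symptoms, classroom functioning and observed behaviour improve after toolkit use and whether this replicates across children. Those children would be counted for or against replication on ratings that cannot support either reading.

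**Working it through.** **Plan's own figures.** Eight schools with 2 to 4 children each give 8 × 2 = 16 and 8 × 4 = 32 children, as stated. The maximum of 32 teachers in Table 1 is one per child. The study states no power calculation, so there is none to reproduce.

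**Inputs from the article.** Study window September 2022 to January 2025; two cohorts of four schools; three consecutive terms per school; rating weeks from Table 3.

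**Assumptions.** Three terms a year, a new class teacher each September, and four different baseline terms within a cohort.

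**Step 1: where September falls.** The window holds 7 full terms (autumn 2022 to autumn 2024). Each school needs 3, so there are 7 − 3 + 1 = 5 possible baseline terms.

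| Baseline term | September falls between |
|---|---|
| Autumn 2022, autumn 2023 | no phases (all three in one school year) |
| Spring 2023, spring 2024 | intervention and follow-up |
| Summer 2023 | baseline and intervention |

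**Step 2: how many schools.** A cohort uses four of the five terms, so it leaves one out.

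| Term left out | Schools crossing at baseline to intervention | Schools crossing at intervention to follow-up |
|---|---|---|
| Autumn 2022 | 1 | 2 |
| Spring 2023 | 1 | 1 |
| Summer 2023 | 0 | 2 |
| Autumn 2023 | 1 | 2 |
| Spring 2024 | 1 | 1 |

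Over two cohorts this gives 0 to 2 schools at baseline to intervention and 2 to 4 at intervention to follow-up. In the natural layout (cohort 1 on autumn 2022 to autumn 2023, cohort 2 on spring 2023 to spring 2024) the counts are 1 + 1 = 2 and 1 + 2 = 3, and 8 − 5 = 3 schools keep one rater throughout. If the cohorts' different entry times mean different first baseline terms, the later cohort must use summer 2023, and the first range narrows to 1 to 2.

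At 2 to 4 children per school, two affected schools hold 4 to 8 children, a quarter of the 16 to 32.

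**Step 3: what the affected series look like.** Table 3 has symptom and functioning ratings in baseline weeks 1, 3, 5, 7, 9, 11 and 13 (7 points) and intervention weeks 2, 4, 6, 8, 10 and 12 (6 points). In a summer-baseline school the first 7 come from one teacher and the next 6 from another. The new teacher's first rating is in week 2, when module 1 strategies start, so no rating by the new teacher precedes them.

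**Step 4: size of the false signal.** Take a child with no toolkit effect and a new rater who scores d within-child SDs lower (better). With independent normal ratings, Tau without trend correction is (improving pairs − worsening pairs) / (7 × 6), with expectation 2Φ(d/√2) − 1. For d = 1 this is 2Φ(0.707) − 1 = 0.52. Simulating 20,000 children per setting with an exact two-sided rank test at 5% gives:

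| Rater shift d (assumed) | 0 | 0.25 | 0.5 | 1.0 | 1.5 | 2.0 |
|---|---|---|---|---|---|---|
| Mean Tau | 0.00 | 0.14 | 0.28 | 0.52 | 0.71 | 0.84 |
| Significant apparent improvement | 2% | 4% | 10% | 30% | 60% | 84% |

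The article gives no figure for between-teacher differences, so d is shown as a range. A shift the other way hides a true benefit by the same amount.

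**Step 5: teacher count.** In the natural layout 5 schools cross a September. With four children each, up to 5 × 4 = 20 receiving teachers come in, or up to 32 + 20 = 52 against the 32 in Table 1 (fewer if a receiving teacher is already enrolled).

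**The case against.** The strongest answer is that the plan does not rest on one school. Design asks for consistent improvement across schools, and Sample size and Subaim C make replication across individuals the test. Autumn- and spring-baseline schools, 6 of 8 in the natural layout, start the toolkit within a school year, so a step seen only in summer-baseline schools would not replicate. Parent SSIS and researcher observation do not depend on the class teacher. Subaim C is secondary and exploratory, in a study that disclaims any test of effectiveness. Figure 1 and the supplement on risks and mitigation are not shown.

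Most of this stands and sets the severity. It does not remove the point: the SWAN is teacher-only, Subaim C names teacher-reported symptoms, and no rule gives parent report or observation precedence when the teacher changes.

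A reader might infer more, in four ways that the document does not support:

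- That every school crossing September can show a false toolkit effect. In spring-baseline schools the switch comes after the intervention and cannot mimic a step at introduction.
- That both outcomes lose their rater altogether. The SSIS subscale also has a parent report.
- That the receiving teacher misses the preparatory toolkit steps that Table 3 places in baseline weeks 11 to 13, or is outside the training criterion. The article does not say so; its definition of staff participants can include a receiving teacher.
- That teacher retention must fail. With 4 to 6 of 8 schools crossing, only 25% to 50% of original teachers would remain to follow-up, below the green threshold of 65%. But the article does not define retention as the original teacher staying.

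**Conclusion.** The point holds for summer-baseline schools: about 2 of 8 in the natural layout, 0 to 2 over the possible layouts. There the SWAN and the teacher SSIS cannot separate a rater change from a toolkit effect, while Design would read the change as pointing to the toolkit. In spring-baseline schools (2 to 4 of 8) only the reading of maintenance is affected.

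This rests on three terms a year, four different baseline terms per cohort and a new class teacher each September. The last is implied only indirectly, by the Year 5 limit; Figure 1 or the supplement could change the counts or already deal with it. The main aims, which rest on the progression criteria and qualitative data, are not undermined, apart from the open question of which teacher is counted. Severity: moderate.

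**What to change.** Keep the term allocation. Allowing only autumn and spring baselines looks simpler but does not fit: it leaves four terms (autumn 2022, spring 2023, autumn 2023, spring 2024), which both cohorts would have to share, against the statement that they enter at different times.

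Instead:

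- Record rater identity with every SWAN and SSIS form, and mark rater changes on the plots.
- Where the rater changed between baseline and intervention, do not count a step on teacher ratings as a replication. Read those children from parent SSIS and researcher observation.
- Where the rater changed between intervention and follow-up, treat the new teacher's ratings as a separate series and not as evidence of maintenance.
- State that the receiving teacher is enrolled, and how that teacher counts in Table 1 and in the training and retention criteria of Table 2.

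The cost is one form field, a plotting convention and a few sentences. The downside is that a few children (4 to 8 in the natural layout) contribute no teacher-rated replication. Parent report and observation remove the change of rater but not the change of class, so even those children need a cautious reading.
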